### Intervention

An interventional cardiologist will perform angiography under the supervision of a senior interventional cardiologist. CCS patients who require revascularization based on the newest guideline [21] will undergo PCI using DES. FFR (Fractional Flow Reserve) ≤ 0.8 or iFR (Instantaneous Wave-Free Ratio) ≤ 0.89 will be considered as evidence of ischemia. PCI will be performed using the radial or femoral approach to achieve complete revascularization of at least one stenosis. All target lesions will be revascularized using the 4th generation DES. Randomization will take place after diagnostic angiography but before stent insertion (Fig 1). Eligible patients will be divided into two groups: the control group, which will get conventional DAPT with aspirin and Clopidogrel (80 mg aspirin once daily, and 75 mg clopidogrel once daily), and the experimental group, which will receive ticagrelor monotherapy (90 mg twice daily) following PCI for six months. Antiplatelet therapy will start before or at the time of PCI. Patients will receive a loading dose of assigned drugs (325 mg for aspirin, 300 mg for clopidogrel, and 180 mg for ticagrelor) before stent insertion unless they are already on pre-PCI maintenance therapy with the mentioned drugs. Peri-procedural aspirin use will not be allowed in the experimental arm.

**Fig 1 pone.0325663.g001:**
[figure not shown]
SPIRIT schedule of study timeline; TICALONE trial. *The interventions in this study involve comparing two groups: one receiving conventional dual antiplatelet therapy (DAPT) with aspirin and clopidogrel as control, and the other receiving ticagrelor monotherapy. Both groups will start their respective antiplatelet therapies at the time of PCI and will continue for six months post-PCI. **The primary efficacy endpoint of the study is a composite of cardiac death, target vessel myocardial infarction (MI), stent thrombosis, and the need for revascularization within 6 months post-PCI. The primary safety endpoint is any Bleeding Academic Research Consortium (BARC) type 3 or 5 bleeding up to 6 months post-PCI. Secondary endpoints include all-cause death, occurrence of major adverse cardiovascular events (MACE), and each component of the primary endpoint at 6 months.

### Modifications

Follow-up visits are scheduled at 1, 3, 6, and 12 months after the PCI procedure. If adverse events occur that require modifications to antiplatelet therapy or hypersensitivity reactions confirmed by the Data Safety and Monitoring Board (DSMB) and Trial Management Committee (TMC), drug consumption will be discontinued. These events will be recorded as study outcomes or adverse events. If the DSMB and TMC adjudicate these events as potentially leading to non-adherence to medication, the intervention group will be switched to standard care. The drugs responsible for these events will be replaced with safe and effective alternatives in both groups. Data from participants who experience such events will be censored at the time of the event to ensure accurate statistical analysis. Dyspnea, the most common side effect of ticagrelor, will be carefully monitored and recorded during follow-up visits. In case of severe dyspnea which may lead to non-adherence to the medication, the patient will be switched from the experimental therapy to the standard regimen. Non-severe dyspnea will be managed using conservative strategies like recommending caffein, theophylline, or inhaled bronchodilator in more severe cases.

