### Outcomes

The co-primary efficacy endpoint is a composite of cardiac death, MI, stroke, stent thrombosis, and the need for revascularization. The secondary endpoints are all-cause death, occurrence of MACE including cardiac death, stroke (ischemic, hemorrhagic, or unknown), MI, arrhythmia, and other component of the co-primary endpoint. The primary safety endpoint is any Bleeding Academic Research Consortium (BARC) bleeding type 3 or 5 after PCI. The secondary safety endpoint is the occurrence of BARC type 1–5 bleeding. Ancillary endpoints are other adverse events including dyspnea, drug adherence, and reaction. All endpoints will be evaluated in each follow-up visit and the results of the analysis of endpoints will be reported at the end of 6- and 12- months post PCI. All events will be adjudicated by DSMB and TMC.

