### Blinding

The allocation of patients to each group is known only to the cardiologist responsible for randomization. This cardiologist is not involved in the patient’s treatment, follow-up, outcome assessment, or data analysis to ensure blinding of the physician team to the allocation. The allocation is stored using a code number in a computer-based data system, which will remain blinded until the analysis is complete. Neither the patients, investigators, nor data analysts will be aware of the group assignment. To ensure the blinding of participants and prevent them from identifying their assigned treatment group, despite differences in the type and number of medications, a standardized method of tablet administration was employed. Following randomization and prior to stent insertion, all patients will receive two unmarked tablets as a loading dose. In the control group, patients will be administered one 325 mg aspirin tablet and one 300 mg clopidogrel tablet. In contrast, patients in the intervention group will receive two 90 mg ticagrelor tablets, administered by the cardiologist responsible for the randomization process. For the maintenance dose, each patient will be provided with two boxes of tablets and instructed to take one tablet from each box daily, one in the morning (8:00 AM) and one in the evening (8:00 PM). In the intervention group, both boxes will contain 90 mg ticagrelor tablets, whereas in the control group, one box will contain 80 mg ASA tablets and the other will contain 75 mg clopidogrel tablets. The same cardiologist responsible for randomization will also distribute the medication boxes containing the required drugs for the six-month follow-up period. This approach is designed to preserve the double-blind nature of the study, ensuring that participants, physicians, outcome assessors, and other study personnel remain unaware of group allocations. In the event of adverse reactions or if a medication switch is deemed necessary by the DSMB or TMC, the group allocation will be unblinded, and appropriate adjustments will be made.

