### Data monitoring, harm, and auditing

Prior to conducting statistical analysis, an expert from the cardiology department, who is not part of the research team, will review and validate all measurements. This adjudicator will examine the quality of each measurement and will omit any that do not meet the required standards, treating them as missing data in the analysis. Additionally, an impartial safety committee, working without knowledge of the treatment assignments, will review and determine any significant MACE. After this adjudication process is finalized, the database will be made accessible for data analysts. The study’s executive committee will communicate any adverse events to a separate DSMB. This board, which operates independently, holds the power to halt the trial prematurely in cases where patient safety is at risk or the main research goal is achieved. If the adverse event rate (primary safety and efficacy endpoint) in the intervention group surpasses that of the control group by more than 20% during any interim analysis, the DSMB will review the data and may recommend termination of the trial if necessary. The DSMB will be responsible for regular safety monitoring, including unexpected serious adverse events, mortality, and severe bleeding, with safety reports generated for review. Additionally, all MACE and bleeding events will be promptly reported to the DSMB, which will conduct independent audits each month. In addition to tracking MACE and bleeding, we will systematically collect data on other potential harms, such as drug reactions, dyspnea, and adverse events, through both spontaneous reporting and structured follow-up visits. Adverse events will be recorded, analyzed, and reported using Common Terminology Criteria for Adverse Events version 4.0 (CTCAE v4.0). All harms, regardless of their frequency, will be reported in publications to provide a comprehensive view of the safety profile. This approach ensures transparency and provides a detailed understanding of the potential risks associated with the interventions.

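### Unblinding is triggered by adverse reactions as such, without a test of clinical need, and stopping for hypersensitivity is worded as following committee confirmation

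*Protocol article*

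**What the plan says.** **Unblinding.** The Blinding section of the protocol article states: "In the event of adverse reactions or if a medication switch is deemed necessary by the DSMB or TMC, the group allocation will be unblinded". The sentence goes on to say that "the group allocation will be unblinded, and appropriate adjustments will be made". The same section describes the masking procedure as "ensuring that participants, physicians, outcome assessors, and other study personnel remain unaware of group allocations".

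**Stopping and switching.** The Modifications section has one sentence with two limbs that lead to discontinuation. The first covers adverse events that call for a change of antiplatelet therapy. The second reads "hypersensitivity reactions confirmed by the Data Safety and Monitoring Board (DSMB) and Trial Management Committee (TMC), drug consumption will be discontinued". The section continues: "If the DSMB and TMC adjudicate these events as potentially leading to non-adherence to medication, the intervention group will be switched to standard care". It also provides for the responsible drug to be replaced by a suitable alternative in either arm, and it has non-severe dyspnea managed conservatively.

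**Who adjudicates and what is reported.** The Outcomes section assigns adjudication of all events to the DSMB and TMC. The section on data monitoring, harm and auditing describes a safety committee that works without knowledge of allocation, and gives it the determination of significant MACE. On reporting, it says that "all MACE and bleeding events will be promptly reported to the DSMB". Other harms are collected separately, "such as drug reactions, dyspnea, and adverse events, through both spontaneous reporting and structured follow-up visits".

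**The concern.** There are two practical rules here, and each gives a worse result than intended if it is followed as written.

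The first is the code-break rule. In a double-blind trial the usual reason to reveal an allocation is that the patient's care depends on it. The article's rule has no such condition: an adverse reaction is enough. Each code break that does not serve care costs some of the blind and gains nothing. Bleeding is the natural place to look, because the article names no blinded committee for it, and minor bleeding within the secondary BARC 1–5 endpoint is the part most open to judgement.

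The second is the stopping rule. For hypersensitivity the wording puts confirmation by two bodies ahead of stopping the drug. The treating team is blinded, and the cardiologist who knows the allocation takes no part in treatment or follow-up. The physician facing a reaction therefore cannot tell which drug is suspect, and the patient has a new stent. A clear order of actions (stop, replace, then review) is worth having in that situation.

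**Working it through.** No arithmetic applies. The article gives no rate of reactions, switches or code breaks, and no time for committee confirmation. The check is a reading of the sections against each other.

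**Step 1: is an adverse reaction a separate trigger?** The Blinding sentence joins two conditions with *or*: adverse reactions, and a switch that the DSMB or TMC considers necessary. If only reactions leading to a switch were meant, the second condition would cover them and the first would add nothing. The closing clause about adjustments describes what follows unblinding. It suggests that a change of care is in mind but does not make it a condition. No grade, seriousness or need-to-know limit appears.

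**Step 2: which patients does the literal rule expose?**

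| Patient with a reaction | Code opened? | Later follow-up |
|---|---|---|
| Drug stopped or switched | Yes, and care may need it | Largely outside the analysis: Modifications censors at the event, and Treatment of missing values excludes time after a switch |
| Stays on study drug | Yes, on the literal wording | Continues to 6 and 12 months and is analysed |

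Only the second row is a problem.

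**Step 3: who assesses later events in the second row?** The DSMB and TMC adjudicate all events, and they are also the bodies that confirm reactions and decide switches. Significant MACE has an explicitly blinded committee. No such committee is named for bleeding, and no sentence keeps a revealed allocation from the adjudicators. The general aim that outcome assessors stay unaware still applies, so the code-break rule works against a stated aim of its own section.

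**Step 4: does another section make confirmation of hypersensitivity immediate?** The prompt-report rule names two event types, MACE and bleeding. Drug reactions are collected by spontaneous report and at structured visits. Other adverse events go to the DSMB with no time stated, and its audits are monthly. The DSMB's remit does include unexpected serious adverse events, so a serious unexpected reaction is within its oversight, but no speed of confirmation follows from that.

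**Step 5: who decides a switch?** Modifications refers to the DSMB *and* TMC (both); Blinding refers to the DSMB *or* TMC (at least one). A decision by both satisfies both sections. They part only when exactly one body decides. The severe-dyspnea sentence names no deciding body and may simply be a case of the general rule.

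**The case against.** The strongest reply is that this is loose drafting in a condensed article. Emergency-stop and code-break procedures commonly sit in the full protocol, and nothing in the article forbids a physician or patient from stopping at once. The first limb of the Modifications sentence already covers adverse events that need a change of therapy, and a hypersensitivity reaction could fall there. Patients are told to contact the clinic with problems and are telephoned monthly. The clause on adjustments points to reactions that need a change of care, and those who stop or switch are censored in any case.

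Much of this stands. It would be wrong to say that the article prohibits stopping before the committees meet: the first limb can be read to allow it. A longer procedure elsewhere would also excuse missing detail. But it would not change the two rules that are stated, one of which attaches confirmation specifically to hypersensitivity while the other makes reactions a trigger on their own. The censoring argument covers patients who stop or switch, not those unblinded while staying on drug.

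A reader might infer that mild dyspnea, the commonest side effect of ticagrelor, would lead to code breaks mainly in that arm. The documents do not support this. The Outcomes section lists dyspnea apart from reactions ("Ancillary endpoints are other adverse events including dyspnea, drug adherence, and reaction"), the harms section also names the two separately, and Modifications manages non-severe dyspnea without mention of unblinding. A reader might also take the *and*/*or* difference as a contradiction of substance. It matters only if one body acts alone, and no consequence for a patient or an analysis is shown.

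**Conclusion.** The concern holds in a limited form and is minor. As written, the Blinding section allows the code to be opened for a reaction that changes nothing in the patient's care. This runs against its own aim, in a trial where the bodies that handle reactions also adjudicate all events and only significant MACE has an explicitly blinded committee. The Modifications section words stopping for hypersensitivity as following confirmation by two bodies, with the reservation that its first limb may allow an earlier stop.

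The size cannot be given in patients or days. A reader might infer that the non-inferiority result is biased, but nothing in the article shows an effect on the primary analysis. The conclusion assumes that staff follow the wording literally and that the full protocol, which is not shown, does not override it.

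**What to change.** **Blinding section.** Limit unblinding to cases where knowing the allocation is needed for the patient's immediate care, and keep the revealed allocation from everyone who adjudicates endpoints, including bleeding. One added phrase can confirm that non-severe dyspnea managed conservatively is not a reason to open the code.

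**Modifications section.** State that the treating physician may stop the suspect drug at once and start the replacement antiplatelet that the section already provides for, with DSMB and TMC review afterwards. Where choosing the replacement requires the allocation, the code break meets the need-for-care test. Stopping and replacing should be stated together because of the new stent.

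**Editorial only.** Name the same deciding body for a switch in both sections; the investigators can choose which. If wished, note in Concomitant care that the replacement is an exception to its ban on other antiplatelets.

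The cost is a few words in two sections, with no change to design, sample size or analysis. Because the wording bears on patient safety and study procedures, it would go through the formal amendment route that the article describes.

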### Adherence

To enhance treatment adherence, the cardiologist will emphasize the importance of taking the study medication as prescribed, including the correct dose, timing, and drug characteristics, during each visit. Patients will also receive detailed instructions about the purpose, use, and benefits of the procedures and pharmacotherapy involved in the study. The cardiologist will remind participants of the importance of contacting the clinic if they experience any issues potentially related to the study, such as bleeding, chest pain, cold sweats, or other related symptoms. Additionally, patients will be asked about any difficulties they may have in taking their study medication.

### Concomitant care

The administration of any antiplatelet or anticoagulant other than study pills is prohibited. The prescription of additional medications for the prevention or treatment of other conditions, according to current guidelines, is permitted only if there is no interaction with the study medications. If a patient requires anticoagulant therapy that interferes with the study drugs due to a specific illness or event, the event will be recorded, and the patient will be censored. At each follow-up visit, patients will be asked about any new medications, illnesses, signs, or symptoms they experience during the study. Medication adjustments will be made as necessary to prevent any impact on the trial results.

### Outcomes

The co-primary efficacy endpoint is a composite of cardiac death, MI, stroke, stent thrombosis, and the need for revascularization. The secondary endpoints are all-cause death, occurrence of MACE including cardiac death, stroke (ischemic, hemorrhagic, or unknown), MI, arrhythmia, and other component of the co-primary endpoint. The primary safety endpoint is any Bleeding Academic Research Consortium (BARC) bleeding type 3 or 5 after PCI. The secondary safety endpoint is the occurrence of BARC type 1–5 bleeding. Ancillary endpoints are other adverse events including dyspnea, drug adherence, and reaction. All endpoints will be evaluated in each follow-up visit and the results of the analysis of endpoints will be reported at the end of 6- and 12- months post PCI. All events will be adjudicated by DSMB and TMC.

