### Participant timeline

After a clear decision to conduct diagnostic angiography for CCS patients based on current guidelines [22,23]. They will be informed about the study and available options. After providing the informed consent, the pre-PCI questionnaire will be completed by an interventional cardiologist and a member of TMC. Patients will be randomized to treatment or control group after diagnostic angiography and before stent insertion. The loading dose of the assigned medications for each group will be administered to the patient prior to stent insertion. After the procedure, the enrolled patients will be visited for evaluation and management of underlying diseases, routine assessments, and optimal medical therapy. Clinical follow-ups will be performed at 1, 3, 6, and 12 months and telephone contacts will be performed every month till the end of the study. An assessment of angina status, cardiovascular drug use, dyspnea, and any serious adverse events will be recorded during these clinical follow-up visits. Illustrative participant timeline is shown in Figs 1 and 2.

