### Statistical analysis

Continuous variables will be presented as mean ± SD and categorical variables will be presented as counts and percentages. The comparison of categorical variables will be conducted using either the χ² test or Fisher’s exact test. To compare continuous variables, the Student’s t-test or the Wilcoxon rank-sum test will be used for non-normally distributed data. The statistical analyses will be carried out using Stata version 18.0 (StataCorp LLC, College Station, Texas, USA). All primary and secondary endpoints will be analyzed both on an intention-to-treat basis, determined by allocation. Cumulative event rates will be estimated with the Kaplan-Meier method. The Cox log-rank approach will be utilized to compare the incidence of endpoints, specifically focusing on the time-to-first-event analyses. Patients lost to follow-up will be censored at the time of the last known contact. The null hypothesis will be evaluated on the intention-to-treat population using inferiority statistics. If the upper limit of the one-sided 95% confidence interval of the difference is less than the prespecified non-inferiority margin of 1%, ticagrelor monotherapy will be considered non-inferior to the conventional 6-month DAPT regimen. A subgroup analysis will be conducted for clinically relevant factors such as age, sex, comorbidities, prior use of aspirin or P2Y12 inhibitors, lesion or procedural characteristics, and other risk indicators. A two-sided test will be used for all hypotheses testing at a 5% significance level. The results of this study will be reported in accordance with CONSORT statement. Statistical analysis and reporting of trial results will follow the estimand framework [24].

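### Endpoint timing is tied to PCI rather than randomisation, so post-allocation events during the index procedure are not clearly counted

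*Protocol article*

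**What the plan says.** **Order of events.** The Intervention section states: "Randomization will take place after diagnostic angiography but before stent insertion". The Participant timeline adds: "The loading dose of the assigned medications for each group will be administered to the patient prior to stent insertion". The Randomization and Blinding sections give the same order. The Intervention section waives the loading dose for patients already on maintenance therapy with these drugs. It also states: "Peri-procedural aspirin use will not be allowed in the experimental arm". The index PCI is therefore done after allocation and under the allocated strategy.

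**Endpoint wording.** In the Outcomes section the safety endpoint carries a start point: "The primary safety endpoint is any Bleeding Academic Research Consortium (BARC) bleeding type 3 or 5 after PCI". The efficacy endpoint in the same section carries none: "The co-primary efficacy endpoint is a composite of cardiac death, MI, stroke, stent thrombosis, and the need for revascularization". The Fig 1 legend places efficacy events in a window described as "stent thrombosis, and the need for revascularization within 6 months post-PCI", and safety as "type 3 or 5 bleeding up to 6 months post-PCI". The abstract names BARC 3 or 5 bleeding as the primary safety endpoint without a time limit.

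**Analysis.** The Statistical analysis section says that endpoints will be "analyzed both on an intention-to-treat basis, determined by allocation", using time-to-first-event methods. It does not say when the clock starts.

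**The concern.** An intention-to-treat comparison protects against bias because everything after allocation is counted in the arm to which the patient was allocated. If the clock starts at the end of PCI, events that happen after allocation but during the procedure drop out of the endpoint.

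These events are relevant here. The Objective section describes immediate monotherapy with no initial dual-therapy period, and the procedure itself is the first part of that exposure. The gap bears mainly on procedural bleeding, MI, stroke and cardiac death. Stent thrombosis needs a stent in place, so little of it can fall in the interval. In a non-inferiority trial judged on an absolute 1% margin, a true excess in one arm that is not counted cannot count against the claim. Even without bias, the people adjudicating events need one rule, and the abstract, the Outcomes section and the Fig 1 legend do not give the same one.

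**Working it through.** **1. The sequence and the windows side by side.** The stated order is: diagnostic angiography, randomisation, loading dose, stent insertion, end of PCI, follow-up. Call randomisation to end of PCI interval A, and everything later interval B.

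| Place | Endpoint | Start point stated | Interval A covered? |
|---|---|---|---|
| Abstract, Methods | Primary safety | None | Not excluded |
| Outcomes | Primary safety | After PCI | No, if read literally |
| Outcomes | Primary efficacy | None | Not excluded |
| Outcomes | BARC 1–5 (secondary safety) | None | Not excluded |
| Fig 1 legend | Both primary endpoints | Six-month post-PCI window | Unclear |
| Statistical analysis | All primary and secondary | None; by allocation | Implied by the principle |

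Interval B is covered in every row. Only interval A is in doubt. The doubt is firmest for the primary safety endpoint. For efficacy it depends on the Fig 1 legend, whose list of components also leaves out stroke, which the Outcomes section includes.

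**2. The plan's own figure.** From the Sample size section: p = 2% in both arms, margin 0.01, one-sided alpha 5%, power 80%.

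n = 2 × ((1.645 + 0.842)/0.01)² × 0.02 × 0.98 ≈ 2,424 per arm. This reproduces the stated number. A change of time zero alters none of these inputs.

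**3. What uncounted events could do to efficacy.** The documents give no share of events for interval A, so the shares below are assumptions.

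*(a) Equal loss in both arms.* The true difference stays at zero. With SE = √(2p(1−p)/2424), power = Φ(0.01/SE − 1.645):

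| Share of the 2% in interval A | Counted rate | Margin as share of counted rate | Nominal power |
|---|---|---|---|
| 0% | 2.0% | 50% | 80% |
| 5% | 1.9% | 53% | 82% |
| 10% | 1.8% | 56% | 84% |
| 20% | 1.6% | 63% | 87% |
| 30% | 1.4% | 71% | 91% |

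*(b) Loss of an excess confined to the ticagrelor arm.* Suppose the true six-month rates are 3% and 2%, exactly at the margin, so that a false claim should occur 5% of the time. With counted difference d, P(claim) = Φ((0.01 − d)/SE − 1.645).

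- 0.2 points hidden: d = 0.008, SE = √((0.02 × 0.98 + 0.028 × 0.972)/2424) = 0.00439, P = 11.7%.
- 0.5 points hidden: d = 0.005, SE = √((0.02 × 0.98 + 0.025 × 0.975)/2424) = 0.00426, P = 31.9%.

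The second case is extreme: it puts half of the whole six-month excess, equal to a quarter of the 2% control rate, inside one procedure. Both cases show how the mechanism works and are not estimates. An excess hidden in the control arm would act in the opposite direction.

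**4. Safety.** The protocol states no expected rate for BARC 3 or 5 bleeding, so no comparable figure can be computed. The direction is open. If aspirin plus clopidogrel caused more procedural bleeding, leaving it out would work against ticagrelor. If ticagrelor caused more, leaving it out would help ticagrelor.

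**5. The initial phase.** At about 180 per arm, 2% gives 3.6 expected efficacy events per arm. One event counted or not moves an arm's proportion by 1/180 = 0.56 points.

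**The case against.** The best defence is that nothing in the protocol tells anyone to discard procedural events. The Fig 1 phrases mainly say when the window closes. The efficacy sentence in the Outcomes section and the safety definition in the abstract have no start point, and analysis by allocation points to counting from allocation. The article also uses post-PCI terms loosely: it describes six months of treatment following PCI, yet says that therapy starts before or at PCI. All of this stands. It makes the point a gap in wording rather than a stated rule to omit events.

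Three stronger readings are tempting, and the documents do not support them.

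- A reader might infer that the whole peri-procedural aspirin-free period is lost. It is not: the interval ends with the procedure, and the aspirin-free hours and days afterwards are counted. The Background remark about where ischaemic risk is highest concerns the acute phases after PCI, which lie inside the endpoint. The objective is six months of immediate monotherapy, not the procedure alone.
- A reader might infer that false non-inferiority becomes easier on both endpoints. For bleeding the direction is not established.
- A reader might take the illustrative percentages as the size of the problem. They rest on assumed shares with no source in the documents.

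The defence does not remove the words in the Outcomes sentence. They attach a post-PCI start to a primary endpoint that is to be analysed from a pre-stent randomisation. Nor is this ordinary condensation in an article: a start point is stated, and it does not match the protocol's own randomisation point.

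**Conclusion.** The point holds in a narrow form. Randomisation and the allocated loading dose come before stenting and analysis is by allocation, yet the primary safety endpoint is worded from PCI onward and the Fig 1 legend uses a post-PCI window for both primary endpoints. Taken literally, BARC 3 or 5 bleeding during the index procedure is not clearly counted. If the Fig 1 window governs efficacy, neither are procedural MI, stroke or cardiac death.

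The gap runs only from randomisation to the end of the procedure. The size of any bias is unknown. For efficacy, an uncounted excess on ticagrelor would favour the non-inferiority claim; for bleeding, either arm could gain. The stated sample size is unaffected. The conclusion assumes that the post-PCI wording would be applied as written; if it is only a calendar label for follow-up, the remedy is the same sentence of clarification.

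**What to change.** In the Outcomes section and the Fig 1 legend, name randomisation as time zero for every primary and secondary endpoint. Count all events from then to 6 months, and to 12 months for the later report, including those during the index PCI, in the intention-to-treat population. Align the abstract with the same definition. Report events from randomisation to the end of the procedure as a separate row, so that readers can see what they contribute.

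State also that randomised patients stay in this analysis whatever the result of the procedure. The exclusion for unsuccessful PCI or non-optimal stent placement can be known only after randomisation on the stated sequence. If applied at that point, it could remove the same patients.

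The cost is a wording amendment. A few procedure-related events that have nothing to do with antiplatelet therapy will enter the endpoint. The time of randomisation must be recorded: the protocol describes a web-based service and a stored allocation code but does not mention a timestamp, so this needs checking. No sample-size input and no clinical rule changes.
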